# A written self-help intervention for depressed adults comparing behavioural activation combined with physical activity promotion with a self-help intervention based upon behavioural activation alone: study protocol for a parallel group pilot randomised controlled trial (BAcPAc)

**DOI:** 10.1186/1745-6215-15-196

**Published:** 2014-05-29

**Keywords:** Behavioural activation, Cognitive behavioural therapy, Depression, Paraprofessional, Physical activity promotion, Physical health, Pilot randomised controlled trial, Self-help

## Abstract

**Background:**

Challenges remain to find ways to support patients with depression who have low levels of physical activity (PA) to overcome perceived barriers and enhance the perceived value of PA for preventing future relapse. There is an evidence-base for behavioural activation (BA) for depression, which focuses on supporting patients to restore activities that have been avoided, but practitioners have no specific training in promoting PA. We aimed to design and evaluate an integrated BA and PA (BAcPAc) practitioner-led, written, self-help intervention to enhance both physical and mental health.

**Methods/design:**

This study is informed by the Medical Research Council Complex Intervention Framework and describes a protocol for a pilot phase II randomised controlled trial (RCT) to test the feasibility and acceptability of the trial methods to inform a definitive phase III RCT. Following development of the augmented written self-help intervention (BAcPAc) incorporating behavioural activation with physical activity promotion, depressed adults are randomised to receive up to 12 sessions over a maximum of 4 months of either BAcPAc or behavioural activation alone within a written self-help format, which represents treatment as usual. The study is located within two ‘Improving Access to Psychological Therapies’ services in South West England, with both written self-help interventions supported by mental health paraprofessionals. Measures assessed at 4, 9, and 12 month follow-up include the following: CIS-R, PHQ-9, accelerometer recorded (4 months only) and self-reported PA, body mass index, blood pressure, Insomnia Severity Index, quality of life, and health and social care service use. Process evaluation will include analysis of recorded support sessions and patient and practitioner interviews. At the time of writing the study has recruited 60 patients.

**Discussion:**

The feasibility outcomes will inform a definitive RCT to assess the clinical and cost-effectiveness of the augmented BAcPAc written self-help intervention to reduce depression and depressive relapse, and bring about improvements across a range of physical health outcomes.

**Trial registration:**

Current Controlled Trials ISRCTN74390532, 26.03.2013.

## Background

By 2020, depression is expected to become the second largest burden of disease globally [1], with up to one third of all depressed patients having episodes that last longer than 2 years [2]. Whilst evidence-based psychological therapies for depression exist [3], unfortunately, some three quarters of those successfully treated for depression will relapse, having at least one further depressive episode [2]. Depression and anxiety are estimated to cost the UK economy £17 billion in lost output and direct health care costs annually, with a £9 billion impact on benefit payments and lost tax receipts [4]. However, the potential costs of depression may be far higher since depression is associated with sustained physical inactivity [5,6] and consequently an increased risk of physical health co-morbidities such as obesity [7,8], diabetes [9], and stroke [10].

Links between depression and physical health [11], and the additional benefits of physical activity (PA) for depression beyond those provided by medication or therapy alone are well established [12]. However, health care services continue to reflect a ‘dualist’ philosophy [13], targeting mental and physical health separately. In a systematic review [14] examining the effectiveness of psychological therapies for treating depression, none of 204 trials reported a measure of PA, at baseline or follow-up. Therefore, little is known about the impact that changes in PA have upon improved mood. Whilst a small number of studies have sought to compare psychological interventions with exercise interventions [15,16], there have been few attempts to integrate PA into evidence-based psychological therapies for depression.

Behavioural activation (BA) potentially represents a key psychological intervention that is capable of being adapted to additionally target physical health outcomes alongside depression. Adopting a systematic and graded approach, BA targets the inertia and behavioural avoidance that often accompany depression. This helps to overcome sources of negative reinforcement that have maintained avoidance whilst exposing the patient once again to sources of positive reinforcement existent within the environment [17]. Whereas different BA models exist, they share a common theoretical underpinning based upon a behavioural model of depression [18].

Results from several systematic reviews [19] have established BA as an evidence-based treatment for depression [3]. Equal effectiveness for the treatment of depression when compared with other psychological interventions, including the package of interventions delivered within cognitive behavioural therapy (CBT) have been reported [19,20]. There have also been proposals to deliver BA for mild-to-moderate depression within a written self-help format [17,19]. This BA format features prominently as a key low-intensity CBT intervention within the Improving Access to Psychological Therapies (IAPT) programme, implemented across England [21,22].

Whilst aiming to increase behaviour, the focus of BA is, however, not conventional upon systematically increasing PA in a manner that could improve physical health outcomes by adopting techniques associated with PA promotion [23]. However, a focus upon improving physical health outcomes within BA may be achieved with only a slight shift in emphasis. For example, following an initial focus upon improving mood, at an opportune moment, the emphasis could be widened to also target physical health outcomes by selectively reinforcing activities that require greater energy expenditure. This shift in emphasis could potentially be facilitated by the augmentation of BA with a model of health behaviour change, such as self-determination theory [24], to help develop behavioural self-regulatory skills.

PA, in the form of exercise, is an evidence-based intervention for depression in its own right [25] and has additional physical health benefits that medication and psychotherapy treatments do not provide when used independently. However, evidence comes from trials involving participants who may be more motivated to do structured exercise sessions, with intensive support. With technological advances, such as accelerometers to capture PA, there is increasing interest in focusing interventions on breaking up sedentary time and increasing overall daily PA to enhance both physical and mental health [26,27]. Such interventions may also have a greater appeal to patients with depression when compared with those involving recommendations for types of structured exercises [3]. Augmenting BA with approaches to facilitate PA could therefore potentially broaden the effectiveness of the intervention when compared to BA alone, and represents an opportunity to address both mental and physical health outcomes. Both BA and PA promotion also seem highly compatible in approach, employing techniques such as self-monitoring, goal setting, and problem solving. All of these techniques have been independently shown to be effective behavioural change strategies [28].

Combining BA with PA promotion may also help to overcome limitations associated with the use of each intervention when used independently. In particular, the combined intervention may help to reduce the rate of depressive relapse that can occur following treatment. For example, following BA alone, up to two thirds of patients recovering from one episode of depression will relapse and have at least one further episode within 12 months [29]. Previous research examining the benefits of PA for depression raise the possibility that augmenting BA with PA promotion may help to reduce depressive relapse and maintain the therapeutic gains arising from the initial use of BA. For example, following successful treatment for depression, relapse rate 6 months post-treatment was 38% following initial treatment with medication alone, reducing to 31% with medication combined with PA and reduced further to 8% with PA alone [30].

### Study aims and objectives

Informed by the new Medical Research Council (MRC) framework for the development of complex interventions [31], the protocol for a phase II pilot randomised controlled trial (RCT) is reported. This study will examine a number of methodological uncertainties to inform the conduct of a phase III RCT to assess the clinical and cost-effectiveness of a combined BA and PA promotion intervention (BAcPAc) to reduce depressive relapse and improve physical health outcomes for adults with depression compared to BA alone, which represents treatment as usual. No prospectively-identified criteria for progression to a main trial have been set.

This pilot RCT does not involve any hypothesis testing and therefore there is no primary outcome. We are interested to test recruitment and retention rates as well as gain qualitative feedback on feasibility and acceptability of the methodology. The specific feasibility outcomes with the method of evaluation for this pilot RCT are shown in Table 1.

**Table 1 T1:** Feasibility outcomes and evaluation

**Feasibility outcomes**	**Evaluation**
1. Feasibility of participant recruitment	Numbers assessed for eligibility, numbers eligible, reasons for ineligibility, reasons for non-participation, and numbers randomised
2. Appropriateness of data collection processes and outcome measures	Number of missing items and follow-up rates
3. Participant understanding of study information	Qualitative process interviews with participants following participation
4. Estimation of sample size to inform a phase III RCT	Differences at follow-up between study arms in the number of participants that reach an ICD-10 diagnosis of depression using the CIS-R [32]
5. Level of study attrition	Study and treatment drop-out rates
6. Estimate of the resources and costs needed to deliver the intervention	Variability in the number, length, and frequency of support sessions provided by psychological wellbeing practitioners
7. Acceptability towards the cognitive behavioural therapy self-help intervention received, and engagement with the BAcPAc intervention	Qualitative process interviews undertaken with participants following participation

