### Sample size

A total of 80 participants (40 participants per arm) will be recruited. This sample size has been informed by the recommended sample size of ~30 participants per arm for estimation of outcome variance [36] and takes into account a 20% attrition rate over the duration of the study.

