### Treatments

For both the BAcPAc (intervention) and BA alone (TAU) study arms, the BA protocol was developed by Richards [17] and represents the protocol implemented as part of the IAPT programme [21,22]. In the BA alone study arm, the BA protocol [17] has been directly transferred into a written self-help format specifically developed and adopted for use within the study (available on request from the authors). The patient works through the written self-help intervention with a maximum of 12 support sessions provided by a PWP [37]. In the BAcPAc study arm, the BA protocol [17] formed the foundation of an extensive development process based upon focus groups and informed by intervention mapping techniques [17] to deconstruct the BA protocol, and then to reconstruct it within a written self-help intervention [37] incorporating additional PA promotion techniques (available on request from the authors).

Interventions are delivered by four PWPs in both recruitment sites, with two randomised to deliver the BAcPAc study arm and two BA alone in both sites. The PWP role was developed as part of the IAPT programme to support low-intensity CBT interventions within a stepped care model of service delivery for patients presenting with depression and anxiety disorders (excluding PTSD and social anxiety) of mild-to-moderate severity [37]. All PWPs involved in the study have successfully completed an accredited PWP training programme based upon the curriculum [38] developed for the IAPT programme.

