#### Assessments

To inform inclusion within a definitive phase III RCT, data on the following assessments will be collected.

i. Diagnosis of depression: ICD-10 diagnosis as a binary (yes or no) outcome by the CIS-R [32].

ii. Symptoms of depression and index of depressive relapse: PHQ-9 [35] based upon an adapted protocol [45].

iii. PA sedentary behaviour and total energy expenditure: assessed using an accelerometer (GENEActiv) worn on the wrist for one week and a 7-day PA recall survey [46].

iv. The Insomnia Severity Index (ISI) [47].

v. Health-related quality of life: Short Form-36 (SF-36 [48]) and EuroQol (EQ-5DL [49]).

vi. Health and social care services use and cost: simplified version of the Adult Service Use Schedule (ADSUS [50]).

vii. Blood pressure: the average of the last two from three measurements taken seated from the left arm following 10 minutes of rest measured using an Omron M7 Monitor.

viii. Body mass index: weight measured using Omron HN286 Digital Scales and height measured using a tape measure.

In addition, general demographic information, including gender, age, ethnicity, marital status, smoking status, postcode, number of dependants, and age of leaving education, is collected from all participants at baseline.

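### Phase III sample size is tied to the observed between-arm difference in CIS-R diagnosis, which a pilot of 80, justified for estimating variance, cannot estimate usefully

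*Protocol article*

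**What the plan says.** Table 1 of the protocol article (Study aims and objectives) pairs each feasibility outcome with its evaluation. Outcome 4 is "Estimation of sample size to inform a phase III RCT", and the one evaluation given is "Differences at follow-up between study arms in the number of participants that reach an ICD-10 diagnosis of depression using the CIS-R". The follow-up visit is not named. The Assessments list confirms the type of variable: "ICD-10 diagnosis as a binary (yes or no) outcome by the CIS-R".

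The Sample size section states "A total of 80 participants (40 participants per arm) will be recruited". It bases this on a "recommended sample size of ~30 participants per arm for estimation of outcome variance" and says the number "takes into account a 20% attrition rate over the duration of the study".

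The same aims section says that the pilot tests no hypothesis, has no primary outcome and sets no progression criteria. The article gives no target or minimum important difference for phase III and no expected diagnosis rate. It does not say that only the control-arm rate would be carried forward.

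**The concern.** Two stated parts of the plan do not fit together. The number of participants is justified for estimating a variance, but the row on phase III size asks for a difference between two proportions. A binary outcome has no separate variance to estimate, because the variance follows from the proportion. The stated justification therefore says nothing about how well the named quantity will be known.

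Sample size varies roughly with the inverse square of the difference, so a noisy difference gives an even noisier planning figure. If phase III were sized on a pilot difference that came out too large by chance, it would be underpowered. If the difference came out at zero or reversed, no size would follow at all. Informing phase III is the declared purpose of this pilot, and no other row of Table 1 deals with phase III size.

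The time point is also open. The abstract lists the CIS-R among measures taken at 4, 9 and 12 months, whereas Table 2, as it reads in the text available, marks it after screening at 4 and 9 months only.

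**Working it through.** **Inputs from the article.** 40 per arm; about 30 per arm for outcome variance; 20% attrition; 1:1 allocation; binary outcome. The article gives no diagnosis rates, so those below are assumptions shown over a range.

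**Step 1: the plan's own figure.** 30 / (1 - 0.20) = 37.5, rounded up to 38 per arm, against 40 stated. In reverse, 40 x 0.8 = 32 completers per arm, which fits a target of about 30. The arithmetic behind 80 is not at fault.

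**Step 2: precision at 32 per arm.** The 95% half-width is 1.96 x sqrt(2p(1-p)/32) for the difference (common rate p) and 1.96 x sqrt(p(1-p)/32) for one arm.

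| Assumed rate p | Difference | One arm |
|---|---|---|
| 20% | ±19.6 points | ±13.9 points |
| 30% | ±22.5 | ±15.9 |
| 40% | ±24.0 | ±17.0 |
| 50% | ±24.5 | ±17.3 |

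With no attrition at all (40 per arm), the half-width of the difference at 50% is still ±21.9 points.

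**Step 3: what the pilot would show.** These are exact binomial probabilities with 32 per arm. The first pair is borrowed for scale from the Background, where "relapse rate 6 months post-treatment was 38% following initial treatment with medication alone, reducing to 31% with medication combined with PA". It concerns relapse in another population, so three larger assumed differences are shown beside it.

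| Assumed true rates (BA alone vs BAcPAc) | True difference | P(zero or reversed) | P(at least double) |
|---|---|---|---|
| 38% vs 31% | 7 points | 0.32 | 0.28 |
| 50% vs 40% | 10 | 0.25 | 0.20 |
| 50% vs 35% | 15 | 0.14 | 0.11 |
| 50% vs 30% | 20 | 0.06 | 0.05 |

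With no true difference (50% in both arms), the pilot still shows a favourable difference, and so yields a finite sample size, with probability 0.45.

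**Step 4: effect on the phase III number.** 50,000 pilots of 32 per arm were simulated, and each observed pair of rates was put into the usual two-proportion formula (two-sided 5%, 90% power, both assumed).

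- True rates 50% vs 40%, true need 519 per arm: the implied size is 147 at the 25th percentile, 582 at the median and 5,373 at the 75th. Only 20% of pilots come within ±50% of the need, and 37% give less than half of it.
- True rates 50% vs 35%, true need 227 per arm: 30% come within ±50%, and 34% give less than half.

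**Step 5: the alternative.** With the difference fixed in advance at, for illustration, 10 points, the need at 90% power is 392 (30% vs 20%), 477 (40% vs 30%) or 519 (50% vs 40%) per arm. Over this range, uncertainty about the rate moves the answer by about a third (519 / 392 = 1.32), not by orders of magnitude.

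**The case against.** The strongest reply is that this is a pilot with no hypothesis test and no progression rule. Outcome 4 is one of seven, and it promises only to inform phase III. No participant, safety decision or pilot result depends on it, and harm arises only if a later protocol adopts the pilot estimate as its target. That stands, and it limits the weight of the point.

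A reader might infer that the plan commits phase III to the pilot's point estimate. The article does not go that far. It gives no formula, and the same counts would also yield the control rate. It could be meant that the rates would be used alongside a clinically chosen difference. That use would be sound, but the row does not say so: it names the difference and nothing else. The point is therefore about what the row states, not about detail left to a fuller document.

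A reader might also infer, from practitioners being split "with two randomised to deliver the BAcPAc study arm and two BA alone in both sites", that the plan wrongly treats participants as independent. The article states no model or variance for this comparison, so independence is neither asserted nor fixed. A design effect would need an assumed intracluster correlation and a settled count of practitioners per arm. No such claim is made here.

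Finally, the probabilities in Step 3 depend on the assumed true effect and fall quickly as it grows. That is fair, and it is why a range is given. The half-widths in Step 2 depend only on the assumed diagnosis rate.

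**Conclusion.** The point holds. The row names a quantity that the stated sample size was not chosen to estimate and cannot estimate usefully. The half-width of about ±20 to ±24.5 points is as large as or larger than the differences of 7 to 20 points considered here. Across those differences, the chance of no benefit or a reversal runs from 0.32 to 0.06, and the chance of at least doubling the truth from 0.28 to 0.05.

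This rests on 32 completers per arm (derived, not stated), assumed diagnosis rates, and independent observations used as a simplification in this calculation. It does not make 80 the wrong number for a pilot, and it does not undermine the other feasibility outcomes. It is a fault that should be corrected in the wording, not one that invalidates the trial.

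**What to change.** Reword the evaluation for outcome 4 so that the pilot supplies:

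- the proportion in the BA-alone arm with an ICD-10 diagnosis, at one named time point at which the CIS-R is actually collected, with its 95% confidence interval (about ±14 to ±17 points from 32);
- the SDs of the follow-up assessments and the attrition rates, both already planned under Statistical analysis.

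State that the phase III target difference will come from a minimum important difference specified in advance. Report the pilot's between-arm difference, as proportions and not counts, with its confidence interval and for description only. Add to the Sample size section the precision that 32 per arm gives: about ±14 to ±17 points for one arm and ±20 to ±24.5 for the difference.

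The cost is a few sentences and a little extra reporting, with no new data or participants. The stated precision will look less flattering.

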## Methods

This protocol is informed by SPIRIT [33] guidance for the reporting of protocols of clinical trials (Additional file 1).

### Study design

This study employs a single (researcher) blind, parallel-randomised controlled trial design with nested mixed methods process evaluation. Subjects are randomised individually in a 1:1 ratio to either a written self-help intervention based upon BA combined with PA promotion (BAcPAc) or a written self-help intervention based upon BA alone, representing treatment as usual (TAU) (Figure 1) [34].

**Figure 1 F1:**
[figure not shown]
Consort diagram.

Participants are being recruited through two IAPT services [21] located in one rural (East and Mid Devon) and one city based location (Plymouth). Both services are located in the county of Devon, South West of England.

### Participant inclusion criteria

Eligible participants are aged 18 and over, with a current episode of depression confirmed using the structured diagnostic Clinical Interview Schedule (CIS-R) [32] and score between 10 and 23 on the Participant Health Questionnaire (PHQ-9) [35] reflecting moderate to moderately-severe depression. Additionally, eligible participants are required to confirm that they can walk continuously and unaided for 5 minutes. Reflecting standard clinical practice, participants are eligible to participate in the study regardless of whether they are currently receiving antidepressant medication, as long as the dose has been stable for at least 28 days prior to recruitment into the study.

